**6. Number of subjects, allotment method**

6.1. Number of subjects

There will be 50 subjects when consumption is started—25 subjects taking the trial product and 25 subjects taking the placebo.

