14.2. Safety analysis set

(1) Adverse events

Subjects who experienced an adverse event and consumed the trial product at least once

(2) Examination values

Subjects who completed all of the trial’s designated schedule and content

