**15. Evaluation methods**

15.1 Evaluating efficacy

(1) Primary outcomes: subjective dry eye symptoms, BUT, keratoconjunctival disorders, Schirmer’s test

(2) Secondary outcomes: functional vision

(3) Efficacy evaluation methods

For each item, values before consumption and at each time point after consumption will be compared between the trial group and the placebo group using a 2-sample t-test. The amount of change from before consumption to each time point after consumption will be compared between the trial group and the placebo group using a 2-sample t-test. Values at each time point after consumption will be compared to values before consumption in each group using a 1-sample t-test.

For the baseline characteristics of patients with dry eye, Student’s t-test (p ≥ 0.05 by the F-test) will be used for comparison of age, and Pearson chi-square test will be used for categorical data of gender and dry eye diagnosis. Repeated measures analysis of variance followed by Tukey's honest significant difference (HSD) post hoc test will be used for analysis of dry eye symptoms. For the biochemical analysis, paired t-tests will be used for within-group comparisons and the F-test, followed by Student’s t-test (p≥0.05 by the F-test) will be used for between-group comparisons (placebo vs. RJ). A p-value of <0.05 was considered statistically significant. 16.2. Evaluating safety

(1) Outcomes

These are adverse events confirmed from interviews and journal entries (subjective symptoms), and abnormal variations in body weight and scientific examination values. For examination values, changes in items will be checked: body weight, systolic blood pressure, diastolic blood pressure, heart rate, and biochemical data.

(2) Evaluation methods

The number of adverse events and abnormal variations will be totaled to create a table. If the same adverse event occurs in the same subject multiple times, it will be treated as one event. To evaluate changes in examination values, measurements before consumption and at each time point after consumption will be compared using a 1-sample t-test. Figures will be displayed as mean ± standard deviation (or standard error). The significance level will be 2-sided 5%.

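### Mean changes in safety examination values are assessed by significance tests, mostly within group, with no RJ-minus-placebo estimate or confidence interval

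*Protocol*

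**What the plan says.** The safety section (numbered 16.2, printed directly after 15.1) lists adverse events and abnormal variations in body weight and scientific examination values as its outcomes. Its evaluation methods have two parts:

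- Adverse events and abnormal variations are counted and tabulated.
- For changes in examination values, "measurements before consumption and at each time point after consumption will be compared using a 1-sample t-test". The section ends: "Figures will be displayed as mean ± standard deviation (or standard error). The significance level will be 2-sided 5" per cent.

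A comparison with placebo appears only for the biochemical analysis, in 15.1(3): an F-test, then "Student’s t-test (p≥0.05 by the F-test) will be used for between-group comparisons (placebo vs. RJ"), with the rule that "A p-value of <0.05 was considered statistically significant". Biochemical data are neither a primary nor a secondary efficacy outcome in 15.1; they are listed as an outcome only under safety. This test therefore serves safety although it stands in the efficacy section.

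Three other places bear on the point:

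- Section 6.1 sets the size: "There will be 50 subjects when consumption is started—25 subjects taking the trial product and 25 subjects taking the placebo".
- Section 14.2(2) limits the examination-value set to "Subjects who completed all of the trial’s designated schedule and content".
- Section 12.2 has the principal investigator decide whether an abnormal change is an adverse event, using the institution's reference values and published criteria.

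No passage names a between-arm difference, a confidence interval or a safety margin for examination values.

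**The concern.** The safety question for a mean change is how far royal jelly moves a value relative to placebo, and how large a shift the data leave open. The planned output does not answer this.

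For weight, blood pressure and heart rate, the named test looks within one arm. It cannot separate an effect of the product from season, regression to the mean or repeated measurement. For the 15 biochemical items there is a placebo test, but its stated result is a p-value set against 0.05.

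At this size, a non-significant result is compatible with a shift that may matter, and a significant one does not say how large the shift is. A report that follows the text could state that no significant changes were seen, and the reader would have no interval with which to weigh that statement.

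**Working it through.** **Inputs from the protocol.** 25 per arm at the start of consumption (6.1); completers only for examination values (14.2(2)), so n is at most 25 per arm; two-sided alpha 0.05 (16.2(2)). The protocol gives no SD, relevant change, margin or power for any examination value, so there is no figure of its own to reproduce.

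**Assumptions.** A true shift of 0.5 SD of the values; 20 completers per arm as an alternative size; before/after correlation ρ of 0.5, 0.7 or 0.8; equal SDs in both arms and at both visits; no shift in the placebo arm.

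**1. Placebo comparison of values (two-sample t-test).** Noncentrality = d × √(n/2), df = 2n − 2.

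- n = 25: 0.5 × √12.5 = 1.77, df 48, critical t 2.011. Power 41.0%, miss rate 59.0%.
- n = 20: 0.5 × √10 = 1.58, df 38, critical t 2.024. Power 33.8%, miss rate 66.2%.

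Sensitivity to the assumed shift at n = 25: the miss rate is 82% at 0.3 SD, 21% at 0.8 SD and 7% at 1.0 SD.

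**2. The same 0.5-SD shift on change scores.** The SD of a change is √(2(1 − ρ)) times the SD of a value, so the standardised shift is d_c = 0.5 / √(2(1 − ρ)). With n = 25, the between-arm noncentrality is d_c × √12.5 (df 48) and the within-group noncentrality is d_c × √25 (df 24).

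| ρ (assumed) | d_c | Between-arm noncentrality | Between-arm miss | Within-group noncentrality | Within-group miss |
| --- | --- | --- | --- | --- | --- |
| 0.5 | 0.500 | 1.77 | 59% | 2.50 | 33% |
| 0.7 | 0.645 | 2.28 | 39% | 3.23 | 13% |
| 0.8 | 0.791 | 2.80 | 22% | 3.95 | 3% |

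The within-group column detects more because it omits the sampling error of the placebo arm. For the same reason it cannot attribute a change to the product.

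**3. What an interval would show.** The 95% half-width for a between-arm difference in values is t(0.975, 2n − 2) × √(2/n).

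- n = 25: 2.011 × √0.08 = 0.57 SD.
- n = 20: 2.024 × √0.10 = 0.64 SD.

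For a difference in change, multiply by √(2(1 − ρ)). At n = 25 this gives 0.57 SD at ρ = 0.5, 0.57 × √0.6 = 0.44 SD at ρ = 0.7, and 0.57 × √0.4 = 0.36 SD at ρ = 0.8. An observed difference of zero would therefore leave a 0.5-SD shift open at ρ = 0.5 but would exclude it at 0.7 or 0.8. A p-value does not display that distinction; the interval does.

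**The case against.** **Safety is not judged by p-values alone.** A reader might infer that p < 0.05 is the only safety criterion. It is not: abnormal variations are counted in a table, and the investigator judges abnormal values against reference values (12.2). This stands, and it limits the point to mean changes. Those two checks work on individual abnormal values and do not measure a mean shift against placebo.

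**The 59% belongs to one test.** A reader might apply it to blood pressure, weight or heart rate. The document does not support that: the only test named for those items is within-group, and for a 0.5-SD shift it is more likely than not to be significant (67%, 87% and 97% at the three correlations). Even for the biochemical test, 59% falls to 39% or 22% if changes are analysed and correlation is high.

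**No sentence equates non-significance with safety.** A reader might infer that the plan will read p ≥ 0.05 as proof of no harm. The protocol nowhere says so, and its objective concerns dry-eye symptoms and ophthalmological results. The point is about what the planned output can show, not about a false conclusion already written down.

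**0.5 SD is arbitrary.** Agreed. The protocol gives no relevant change, and the miss rates move widely with the assumption.

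**Intervals and interpretation are often left to an analysis plan, and a margin is unusual in a 50-person food trial.** The part about the margin stands, and none is asked for. The part about the analysis plan stands only in part: 16.2(2) and 15.1(3) do fix a method, and an analysis plan consistent with them would still lead with significance tests. It is also true that a reader given mean ± SD and n per arm could compute an interval for the difference in values. An interval for the difference in change also needs the SD of the change, which the text does not promise.

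**Conclusion.** The point holds in a limited form. For mean changes in examination values, the protocol fixes significance tests as the method, within group in 16.2(2) and against placebo only for biochemical data in 15.1(3), with no between-arm estimate or interval. With at most 25 completers per arm, neither a significant nor a non-significant p-value shows how large a difference from placebo is excluded.

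The size depends on the assumed 0.5-SD shift. The biochemical placebo test misses it 59% of the time on values at 25 per arm and 66% at 20 per arm; on change scores at 25 per arm the range is 59% to 22% over correlations of 0.5 to 0.8. The within-group test misses 33% to 3% over the same range but is uncontrolled. The correlations, the shift and the figure of 20 completers are assumptions; only the 25 per arm, the completers-only set and the 5% level come from the document.

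**What to change.** In section 16.2(2):

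1. Make the main summary for each examination value and each post-consumption visit the RJ-minus-placebo difference in change from before consumption, with its two-sided 95% CI. By the schedule, that is weeks 4 and 8 for weight, blood pressure and heart rate, and week 8 for biochemical data.
2. Lay out the planned table of abnormal variations by arm.
3. Label p-values for examination values as descriptive, including those from the biochemical analysis in 15.1(3).
4. Add a sentence that a non-significant result will not be read as absence of an effect on safety values.

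No numerical safety margin is needed. The cost is a few lines of text and one table column, using data already collected. The small downside is that the intervals will be wide, about ±0.57 SD for values at 25 per arm, so the safety statement becomes less favourable. The change makes the uncertainty visible; it does not make the trial more precise.

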16.3. Compliance with, changes to, deviations from, or revisions to the trail protocol

The primary investigator will comply with the trial protocol and not deviate from, or change it without first obtaining the written consent of the trial sponsor. Moreover, if the trial protocol is changed after being approved by the ethics committee, the changes will need to be reapproved by the ethics committee.

However, this does not apply to a situations involving urgent danger to a subject, scenario’s that are medically unavoidable, or circumstances related to clerical matters (example: changing a phone number).

**17. Filling out case report forms**

The primary investigator will fill out a case report form on each subject’s results. These will be signed or stamped, and then submitted to the trial sponsor. Data on the case report form should not contradict the original materials. In addition, personal information should not be included without the subject’s consent.

**18. Ethics**

18.1. Subject selection

The following areas will be considered when selecting the subjects: human rights protections; the trial protocol’s inclusion and exclusion criteria; the subject’s health status, age, sex, ability to give consent, dependence on the principal investigator, and participation in other trials; and whether it is appropriate to ask the subject to participate in this trial.

People who lack the ability to provide consent will not be selected as subjects. When selecting people who could experience some kind of unfair disadvantage from not participating in the trial, full consideration will be given to ensure their consent is being given voluntarily.

18.2. Declaration of Helsinki and ethical guidelines for epidemiological research

This trial will be conducted by following the spirit of the Declaration of Helsinki and according to ethical guidelines for epidemiological research.

18.3. Dealing with subjects whose health is harmed

If a subject’s health is harmed by participating in this trial, the principal investigator will provide whatever therapies or treatments are necessary. However, this does not apply to damage caused by intentionally by a subject or one that is secondary to their mistake. The trial sponsor will obtain insurance and other necessary measures so that they can fulfill their responsibilities.

18.4. Explanation of results

After the trial ends, the subjects may obtain an explanation of the examination and other results from the principal or co-principal investigator.

**19. Viewing original materials**

If a person in charge of the matter from the trial sponsor wishes to check the surveys or other records, the principal investigator and trial institution will allow the surveys and original materials (original copies of consent forms, journals and other records submitted by the subjects, data recorded on case report forms) to be viewed. However, privacy protection will be given full consideration when viewing original materials that contain personal information.

**20. Payments**

21.1. Costs of the trial

This trial will be paid for by a research grant (Yamada Bee Farm research support fund).

21.2. Cooperation payments

The subjects will be given cooperation payments calculated based on the rules of the trial institution.

**21. Storage of records**

21.1. Chief of the trial institution

The chief of the trial institution will store all documents related to the trial for 5 years after the trial is terminated or ends. These documents include original materials (original copies of consent forms, journals and other records submitted by subjects, data recorded on case report forms), contracts, documents related to ethics committee screenings, and other clerical documents related to the trial, such as records on managing the trial product. However, if the trial sponsor requires a longer storage period, the storage duration and methods will be discussed. Moreover, if the trial institution has rules concerning the storage of records, these rules will be followed.

21.2. Principal investigator

The principal investigator will store all records related to the trial according to instructions given by the chief of the trial institution.

**22. Disposal of records**

Once the storage period has passed, consent forms and other materials signed by the subjects will be disposed of properly (incineration, etc.). Anonymized records can be disposed of as is (incineration, etc.).

**23. Planned trial duration**

May 2014 to March 2015

End
